### Study design

2.1.

Nondemented older adults, including those with MCI (≥65 years) who do not have regular exercise habits will be recruited via local advertisements in Hakusan-city, Ishikawa Prefecture, Japan. This is an open label 1-year double-arm study that will be conducted in geriatric clinics and senior day care center in Japan. Figure 1 illustrates the study’s time course and Figure 2 shows flow chart of participants. Older adults will undergo the MCI screen which is used to detect patients with MCI, and all subjects with scores both above and below the cutoff of MCI screen except for subjects with dementia will be encouraged to participate in exercise classes.

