#### Primary outcome measures

2.4.1.

The primary outcome is the program’s efficacy in preventing cognitive decline, as assessed by changes in the memory performance index (MPI) scores of the MCI screen between the screening and 5-month and 1-year follow ups. We will compare between exercise participants and nonparticipants.

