#### Exploratory examination

2.4.3.

For participants whose MPI is below the cutoff score at the screening or follow-up, a mini-mental state examination-Japanese (MMSE-J), brain MRI, ^123^I-iodoamphetamine (IMP)-cerebral blood flow single photon emission computed tomography (SPECT), and blood chemistry analysis [hemoglobinA1c, thyroid hormone, *Treponema pallidum* (TP) antigen STS test, TP antibody LA test, folic acid, vitamins B1 and B12] will be performed to elucidate the underlying disease of cognitive decline. Furthermore, subjects relevant to ≥1 of the following items are recommended for additional examinations: (i) low scores on the MMSE-J (<26 points) or zero points in the delayed recall sub-item, (ii) abnormality of disease-specific region on ^123^I-IMP-SPECT, such as the posterior cingulate, precuneus, and occipital lobe, (iii) hippocampal atrophy (>1.8 on the Voxel-based Specific Regional analysis system for Alzheimer’s Disease: VSRAD), (iv) severe leukoaraiosis. The additional examinations will include the Wechsler Memory Scale-Revised (WMS-R), ^11^C-Pittsburgh compound-B (PiB)-positoron emission tomography (PET), and ^18^F-fluorodeoxyglucose (FDG)-PET to diagnose the underlying diseases, including AD, vascular dementia (VaD), and Dementia with Lewy bodies (DLB).

We will investigate the relationships between program’s efficacy on cognitive function and amyloid pathology (positive or negative of PiB-PET) or arteriosclerotic factors (hypertension, diabetes mellitus, and dyslipidemia). We will also explore the association between the results of various examination such as brain MRI, ^123^I-IMP-SPECT, ^11^C-PiB, and ^18^F-FDG-PET and the progression of cognitive decline.

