### Sample size and statistical considerations

2.6.

Assuming an alpha error of 5% (*α* = 5%) and a difference between intervention participants and nonparticipants groups exercise program values of *d* = 0.5, the required sample size for an 80% power is 64 participants per group. Considering a 20% expected loss to follow-up, the final sample size should be 160.

For comparisons between baseline and follow-up, repeated measures ANOVA will be used. The level of statistical significance will be 0.05. Data will be analyzed using the Statistical Package for the Social Sciences software (version 28; SPSS Inc., Chicago, IL, United States).

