The novelty of our study is to examine whether the exercise program is able to reduce the risk of cognitive decline in older adults with MCI due to AD according to biomarkers. We will investigate the association between AD biomarkers and progression of cognitive decline in this trial. High levels of cerebrospinal fluid (CSF) total tau levels and low levels of CSF amyloid-β_1–42_ were reported to be predictors of rapid cognitive decline in AD (Koch et al., 2013). In the Amyloid Tau Neurodegeneration (ATN) framework, amyloid positive in PiB-PET and low levels of CSF amyloid-β_1–42_ are amyloid markers, and AD findings of FDG-PET and hippocampal atrophy in MRI as well as high levels of CSF total tau are neurodegeneration markers. It was also reported the potential link between atherosclerosis and amyloid metabolism (Martorana et al., 2015). We will clarify the association between amyloid pathology, the presence of arteriosclerotic factors, and the exercise program’s efficacy in cognition.

A major limitation of this study is its nonrandomized control design. However, we hope to demonstrate that starting and continuing physical exercise can prevent cognitive decline and improve physical function in older adults. Additionally, we will elucidate the proportion of MCI due to AD with amyloid biomarker among community-dwelling older adults with MCI.

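### The primary comparison of exercise participants with nonparticipants is nonrandomized, yet the only method named is repeated measures ANOVA, with no stated control of confounding

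*Protocol article*

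**What the plan says.** Section 2.1 (Study design) recruits nondemented people aged 65 or over. After the MCI screen, all of them, above or below its cutoff "except for subjects with dementia will be encouraged to participate in exercise classes". No rule for allocating people to the two arms is given in the text.

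Section 2.4.1 (Primary outcome measures) defines the outcome by "changes in the memory performance index (MPI) scores of the MCI screen between the screening and 5-month and 1-year follow ups" and adds: "We will compare between exercise participants and nonparticipants".

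Section 2.6 (Sample size and statistical considerations) sizes the trial on "a difference between intervention participants and nonparticipants groups exercise program values of *d* = 0.5", with 5% alpha, 80% power, 64 per group and 160 in total after 20% loss. It then names one method: "For comparisons between baseline and follow-up, repeated measures ANOVA will be used".

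Section 3 (Discussion) states: "A major limitation of this study is its nonrandomized control design". It attaches no analytic remedy, and goes on to hope for a demonstration that exercise can prevent cognitive decline.

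Section 2.4.3 (Exploratory examination) brings in other factors, beginning "We will investigate the relationships between program’s efficacy on cognitive function and amyloid pathology" and continuing to hypertension, diabetes and dyslipidemia. These are exploratory questions about the program's efficacy, with no method named. They are not described as adjustment of the primary comparison.

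**The concern.** When everyone is encouraged to join and the comparison group is those who did not, the groups may differ in age, health, motivation and cognition before the program starts. The article recognises the design weakness, but the one method it names does nothing specific about it.

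Two routes to a false result matter here.

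- **Different expected change.** If joiners are younger or have better vascular health, their MPI may decline less over a year whatever the program does. Comparing changes between groups carries that difference straight into the estimate.
- **Regression to the mean.** The MCI screen is done at screening, before people join, and the same score is the reference for change. If people with low observed scores are more likely to join, part of their later rise is a return toward their usual level.

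At stake is the meaning of the primary result. It could be significant with no exercise effect, or a real effect could be hidden, since the bias can run in either direction.

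**Working it through.** **1. The plan's own figure.** Inputs from section 2.6: d = 0.5, alpha 5% (taken as two-sided), power 80%, loss 20%.

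- Normal approximation: n = 2 × (1.960 + 0.842)² / 0.5² = 62.8, so 63 per group.
- Exact two-sample t-test: 63.77, so 64 per group, with power 0.801 at 64.
- Inflation for loss: 128 / (1 − 0.20) = 160.

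Both stated figures reproduce. A one-sided test would give 50. The calculation is that of a plain two-group t-test, in which any difference between the groups is attributed to the program.

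**2. What the group-by-time term does.** For two time points, the group-by-time test in a repeated measures ANOVA is equivalent to a t-test comparing mean change between groups. A constant level difference cancels in the change. A difference in expected change does not.

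**3. Effect of selection bias on the test.** Assumptions: no true program effect, 64 analysed per group, two-sided 0.05. Selection shifts the participants' change by b SD of change in the favourable direction. The documents give no value for b, so a range is shown. The noncentrality is b × √(64/2) = 5.657b, on 126 degrees of freedom, and the favourable rejection rate is the upper tail beyond t = 1.979.

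| Assumed b (SD of change) | Noncentrality | Probability of a significant benefit |
|---|---|---|
| 0 | 0 | 2.5% |
| 0.1 | 0.57 | 8.1% |
| 0.2 | 1.13 | 20.1% |
| 0.3 | 1.70 | 39.1% |
| 0.5 (the planned effect) | 2.83 | 80% |

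**4. Whether adjustment helps.** This was simulated with 4,000 runs per setting, 64 per group and no program effect. A single measured confounder differed by 0.5 SD between groups and had an effect of 0.4 SD on change. The unadjusted estimate was biased by 0.198 SD and the two-sided rejection rate was 0.196. Adjusting for that confounder gave a bias of −0.002 and a rejection rate of 0.051. Over gaps of 0.25 to 0.8 SD and effects of 0.2 to 0.6 SD, unadjusted rejection ran from 0.055 to 0.784 and adjusted rejection from 0.041 to 0.052.

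**5. Regression to the mean.** Assume that joining depends on the observed screening score, that joiners score g SD lower, and that the test-retest correlation is r, with equal variances at both times. The SD of change is √(2(1 − r)), so the spurious benefit in SD of change is (1 − r) × g / √(2(1 − r)).

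| r | g = 0.3 | g = 0.5 |
|---|---|---|
| 0.5 | 0.15 | 0.25 |
| 0.7 | 0.12 | 0.19 |
| 0.9 | 0.07 | 0.11 |

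In simulation at r = 0.7, the change-score test rejected 9.9% (g = 0.3) and 18.5% (g = 0.5) of the time. Conditioning on screening MPI gave 4.5% and 4.8%.

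**6. The opposite mechanism.** If joiners instead differ by g in stable true level, the change score is unbiased and conditioning on a noisy screening score introduces the bias. With r = 0.7 it is −(0.3 × 0.3)/√0.6 = −0.12 for g = 0.3 and −(0.3 × 0.5)/√0.6 = −0.19 for g = 0.5: the same size with the opposite sign. The documents do not say which mechanism applies.

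**The case against.** The strongest reply is that this is a short journal article. It nowhere calls the ANOVA unadjusted, and a covariate list may sit in a full protocol or analysis plan that is not shown. It also discloses the nonrandomized design openly. This stands in part: the word unadjusted is an inference, and so is self-selection, because the text gives no allocation rule and the flow chart is not visible. But the article does not leave the method open. It names one for a comparison whose main weakness it identifies itself, and that method does not address the weakness. Disclosure does not control confounding.

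The quoted sentence speaks of baseline against follow-up, so it may not be meant as the between-group test. If so, the primary comparison in section 2.4.1 has no method attached, and the need to state one is the same.

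A reader might infer three stronger things that the documents do not support:

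- **That an unadjusted ANOVA is the only planned analysis.** It is the only method named; exploratory relationships are also planned.
- **That conditioning on screening MPI always cures regression to the mean.** It does so only if joining depends on the observed score. Otherwise it can add a bias of the same size in the other direction.
- **That the trial will be biased by a known amount.** Every bias size, gap and correlation above is assumed.

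It is also fair that a long adjustment list would be unwise. MCI status taken from the screen largely repeats MPI, since it is MPI cut at 50.2. Regular exercise should vary little among people recruited for lacking it. The article also does not show that nonparticipants have the baseline physical and body-composition tests.

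**Conclusion.** The concern holds in this form: for a primary comparison that the article itself calls nonrandomized, the stated analysis contains no control of confounding. As written, a between-group difference in MPI change could not be separated from differences in who takes part. The sample-size arithmetic is sound and is not part of the criticism.

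The size depends on the unknown selection bias. At 0.2 to 0.3 SD of change, a program with no effect would appear significantly beneficial about 20% to 39% of the time at 64 per group, against 2.5%. Those figures show how sensitive the test is; they are not evidence that bias of that size exists. The conclusion also rests on reading participation as voluntary and the ANOVA as having no covariates. Both are the natural reading, but neither is stated.

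**What to change.** Replace the analysis sentence in section 2.6 with a prespecified plan, fixed before outcome data are analysed:

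- **Primary analysis:** a between-group comparison of change in MPI from screening to 1 year, adjusted for age, sex, screening MPI, and hypertension, diabetes and dyslipidemia from the medical history, plus education if it is collected. Confirm that each item is available in both groups. The MCI screen and the medical history questionnaire are scheduled at screening, and age is an entry criterion.
- **Sensitivity analyses:** (a) a propensity-weighted analysis; (b) a change-score analysis with the same covariates but without conditioning on screening MPI. Report both beside the primary result, because the choice between change score and baseline conditioning depends on how people select into exercise.
- **Further covariates:** add baseline physical measures only if nonparticipants also have them.
- **Conclusion:** word it as an association adjusted for measured factors, and bring the corresponding sentences of the Discussion into line.

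The cost is small. Six covariates take the residual degrees of freedom from 126 to 120 with 128 analysed (119 with education), plus some analysis work. What the fix cannot buy is protection from unmeasured confounding: motivation to exercise would remain, and the report should say so.

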## Discussion

3.

Physical exercise is a promising intervention with strong potential to prevent or delay the onset of cognitive decline and physical frailty in older adults. Our study aims to assess the impact of a novel exercise program on older adults’ cognitive and physical function. We expect that older adults who complete the exercise program will show better cognitive and physical function than those who do participate in the exercise program. Moreover, we expect that our newly developed exercise program will be easy to start and continue for older adults. The one-year follow-up period may seem to short, however, it was reported that aerobic exercise training improved memory 6-months and 1-year after intervention (Erickson et al., 2011). Therefore, we believe we can achieve the primary outcome, which is the program’s efficacy on cognition, by comparing between exercise participants and nonparticipants in a1-year follow-up.

The multi-domain intervention studies have demonstrated mixed outcomes (Ngandu et al., 2015; van Charante et al., 2016; Andrieu et al., 2017). The large-scale open label, 6-year multidomain cardiovascular intervention trial with people aged 70–78 years old (*n* = 3,526) (van Charante et al., 2016), and the Multidomain Alzheimer Preventive Trial (MAPT) using polyunsaturated fatty acids, cognitive training, physical activity for 3 years with people aged 70 years old and over (*n* = 1,689) (Andrieu et al., 2017) both had no significant effects on cognitive decline; whereas the Finnish Geriatric Intervention Study to Prevent Cognitive Impairment and Disability (FINGER) trial demonstrated the effectiveness on delaying cognitive decline (Ngandu et al., 2015). This 2-year randomized controlled trial obtained 1,260 people with 60–77 years old. In our study, we will examine the effect of regular exercise on the prevention of cognitive decline.

The novelty of our study is to examine whether the exercise program is able to reduce the risk of cognitive decline in older adults with MCI due to AD according to biomarkers. We will investigate the association between AD biomarkers and progression of cognitive decline in this trial. High levels of cerebrospinal fluid (CSF) total tau levels and low levels of CSF amyloid-β_1–42_ were reported to be predictors of rapid cognitive decline in AD (Koch et al., 2013). In the Amyloid Tau Neurodegeneration (ATN) framework, amyloid positive in PiB-PET and low levels of CSF amyloid-β_1–42_ are amyloid markers, and AD findings of FDG-PET and hippocampal atrophy in MRI as well as high levels of CSF total tau are neurodegeneration markers. It was also reported the potential link between atherosclerosis and amyloid metabolism (Martorana et al., 2015). We will clarify the association between amyloid pathology, the presence of arteriosclerotic factors, and the exercise program’s efficacy in cognition.

A major limitation of this study is its nonrandomized control design. However, we hope to demonstrate that starting and continuing physical exercise can prevent cognitive decline and improve physical function in older adults. Additionally, we will elucidate the proportion of MCI due to AD with amyloid biomarker among community-dwelling older adults with MCI.

## Dissemination

4.

The results of our study will be presented in peer-reviewed journals. We have a plan to publish secondary analyses of our study and present at international conferences. We will also present the main results to our participants. For Original Research Articles, Clinical Trial Articles, and Technology Reports the Introduction should be succinct, with no subheadings. For Case Reports the Introduction should include symptoms at presentation, physical exams and lab results.

## Ethics statement

The research protocol was approved by the Ethics Committee of the Kanazawa University Medical Ethics Review Board (approval number 114156–1) and was conducted under the Declaration of Helsinki. All participants provided written informed consent for participation. The trial was registered, and a study protocol was uploaded to the Japan Registry of Clinical Trials with the identifier jRCT 1,040,220,140. The protocol employs relevant standard protocol items for clinical trials according to the CONSORT statement.

